## 1. Title

Clinical research of effectiveness and economic feasibility of Chuna manual medicine for temporomandibular disorder: A multicenter randomized controlled trial

## 3. Participants

### 3.1. Participants

Patients with chronic unilateral or bilateral temporomandibular joint (TMJ) and facial pain due to temporomandibular disorders, diagnosed as myofascial TMD by a Korean Medicine Doctor

### 3.2. Inclusion criteria

- 1) Unilateral or bilateral TMD
- 2) NRS for TMD pain (more severe side for bilateral TMD) of 4 or above
- 3) Continuous or intermittent TMJ pain lasting more than 3 months
- 4) Diagnosed as myofascial TMD, Axis I: Group 1 in RDC/TMD criteria
- 5) Aged 19–70 years at the signing of the participant agreement form
- 6) Agreement to participate in the clinical trial, and signing of the agreement form

### 3.3. Exclusion criteria

- 1) The symptoms originated from or were precipitated by a traumatic injury (i.e. traffic accident)
- 2) Patients with TMD but not included in Axis I: Group I of the RDC/ TMD criteria
- 3) Medical history of surgical operations related to TMJ
- 4) Other diseases that can affect the effectiveness and results of the treatment, such as rheumatoid arthritis, neoplastic disease, cerebrovascular accident, myocardial infarction, etc.
- 5) Current assumption of oral medications that can affect the results of the study, such as steroids, immunosuppressive drugs, psychiatric medications, etc.
- 6) Assumption of medications that can affect pain severity, such as non-steroidal anti-inflammatory drugs (NSAIDs), during the last week, or treated with CMT within the last 2 weeks, for any reason
- 7) Pregnant, planning to have babies or currently breastfeeding
- 8) Participated in other clinical trial within a month from the date of screening, or planning to take part in other trials during the period of this study
- 9) Other conditions investigators consider unfit to this trial

### 3.4. Discontinuation and Withdrawal Criteria

Patients have the right to voluntarily withdraw from participating in the clinical study at any time, regardless of the reason. Additionally, the investigator has the authority to discontinue a patient's participation in the study.

Reasons for withdrawal from the clinical study may include, but are not limited to, the following:

- Withdrawal of consent by the study subject
- Medical conditions deemed to jeopardize the safety of the patient if the study continues
- When discontinuation of participation is in the best interest of the patient
- Non-compliance with clinical study regulations by the study subject

Efforts will be made to obtain information on patients who discontinue the clinical study, and the reasons for discontinuation of treatment or observation will be recorded. For study subjects whose participation is discontinued, follow-up may continue with patient consent. However, in the event of withdrawal of consent, follow-up will not be conducted, and patients who discontinue participation in the clinical study will not be replaced.

At any time during the clinical study, if a serious adverse event or an adverse reaction deemed harmful to the

study subject is observed, and if subsequent evaluation of the course and causality of the adverse event with the treatment determines that continuation of treatment is harmful to the study subject, the investigator will permanently discontinue the treatment for the patient in this clinical study.

- Study subjects who discontinue before starting treatment are considered screening failures. Unless medically necessary, all required assessments at the time of discontinuation (screening failures) do not have to be completed.
- Subjects who withdraw early due to adverse events may receive appropriate treatment for the adverse events if necessary. In the case of early withdrawal due to adverse events, the investigator or an investigator designee must continuously evaluate the study subject until the adverse event resolves or is deemed permanent.

Other reasons for discontinuation of the clinical study by the investigator include:

- If a disease that could affect the outcome of the study is discovered in the study subject that was not detected in pre-study screening.
- If there are issues performing medical procedures for temporomandibular joint disease in the study subject.
- If the study subject undergoes surgery, procedures, or treatments with drugs that could affect the study outcome without the direction of the attending physician during the treatment period or follow-up period.
- If the investigator deems that the continuation of the study is inappropriate for any other reason.

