#### **6.3.2 General principles of analysis**

- This study analyzes the results of pain intensity scale, functional scale, quality of life, and cost data for patients who meet the inclusion criteria in a randomized controlled trial.
- The primary analysis will use the ITT (Intention-to-Treat) approach, evaluating all subjects who received at least one treatment. Additionally, the PP (Per-Protocol) analysis will be conducted alongside, evaluating only those subjects who completed the clinical study without dropping out. Missing data will be handled primarily through Multiple Imputation, and LOCF (Last Observation Carried Forward) will be used for sensitivity analysis.
- The socio-demographic characteristics and treatment expectancy of the study subjects will be evaluated by group. Continuous variables will be expressed as mean (standard deviation) or median (interquartile range) and compared between the two groups using Student's t-test. Categorical variables will be expressed as frequency (%) and analyzed using the chi-square test or Fisher's exact test.
- The efficacy evaluation variables of this clinical study are the differences in the changes of continuous outcomes (VAS, NRS, MMO, K-BDI-2, JFLS, SF-12, EQ-5D-5L, EQ-VAS) between the two groups from baseline to each time point. ANCOVA (Analysis of Covariance) will be performed with the baseline values of each variable and the covariate factors that show statistical differences between the

treatment groups at baseline as covariates, and the group as a fixed factor. RM ANOVA (Repeated Measures ANOVA) will be conducted to test the differences in trends at each visit.

- To compare the total amount of differences in each outcome within the period (evaluation time point after treatment completion (5 weeks)) and the entire study period (6 months), the areas under the curve (AUC) at each time point after randomization will be calculated and compared using Student's t-test.

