### **15.2. Deviation from the Clinical Study Protocol**

Investigators and staff must fully understand and strictly adhere to the protocol to prevent violations. To comply with the visit schedule, the staff must take appropriate actions, such as providing written notifications or conducting telephone monitoring for the next visit time. In case of unavoidable protocol violations, the following procedures will apply:

Serious Protocol Violations: For significant violations such as subject withdrawal/drop-out criteria, subject inclusion/exclusion criteria violations, failure to obtain consent, or mid-study drop-out criteria, subjects may be dropped from the study after consultation with the investigator.

Minor Violations: Minor violations must be accurately recorded along with the reasons and extent of the delay, and their impact on the clinical study will be considered during the result analysis.

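### Treated subjects can be removed for non-compliance, outside treatment or protocol violations without the Week 5 VAS being required, although the primary analysis still counts them

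*Protocol*

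**What the plan says.** Protocol 3.4 states that "the investigator has the authority to discontinue a patient's participation in the study". Its listed reasons include "Non-compliance with clinical study regulations by the study subject". A further list in the same section adds unsanctioned surgery, procedures or "treatments with drugs that could affect the study outcome without the direction of the attending physician", in either the treatment or the follow-up period, and closes with a general discretionary ground.

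On what happens afterwards, 3.4 makes three statements:
- A general one: "Efforts will be made to obtain information on patients who discontinue the clinical study".
- A permissive one: "For study subjects whose participation is discontinued, follow-up may continue with patient consent". Follow-up ends if consent is withdrawn.
- A mandatory one, limited to early withdrawal for an adverse event: the investigator or a designee "must continuously evaluate the study subject until the adverse event resolves or is deemed permanent".

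Protocol 15.2 adds that for serious violations, eligibility violations among them, "subjects may be dropped from the study after consultation with the investigator".

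On analysis, 6.3.2 (repeated in section 1.1 of the appended Statistical Analysis Methods) says: "The primary analysis will use the ITT (Intention-to-Treat) approach, evaluating all subjects who received at least one treatment". Missing data go to multiple imputation, with LOCF as sensitivity analysis. Section 6.1 sets the primary endpoint as the VAS five weeks after allocation. The timetable has no assessment for a subject who stops early.

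**The concern.** An analysis of everyone treated is only as good as the outcome data behind it. If a subject who misses sessions, or is found ineligible after the second session, can be taken out of the study while still willing to attend, the primary value is missing because of a conduct rule and not because it could not be obtained.

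The grounds for removal are also not neutral. Poor attendance may reflect lack of benefit or discomfort. Section 5.5.3 prohibits direct treatment of TMJ pain, apart from rescue acetaminophen, until Week 5, so a subject driven to other care by pain can be removed on that ground before the endpoint. Under 5.2.2 only assessors are blinded, so the discretion lies with staff whom the plan does not blind. Missingness may then depend on arm and on pain, and part of the primary result would rest on imputation in place of obtainable data. A later analysis plan cannot recover values that were never collected.

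**Working it through.** **Step 1: follow one subject through the text.** A subject is randomised, receives two sessions, and is then found to breach an eligibility criterion or misses further sessions.

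| Question | Source | Answer |
|---|---|---|
| Can study participation be ended? | 3.4, 15.2 | Yes, at discretion |
| Must the Week 5 VAS be taken? | 3.4, timetable | No; permitted, with consent |
| Is an outcome or visit named in the promise of effort? | 3.4 | No |
| Does the mandatory evaluation apply? | 3.4 | Only to adverse-event withdrawals, and for safety |
| Is the subject in the primary analysis? | 6.3.2 | Yes, having been treated |
| How is the missing value handled? | 6.3.2 | Multiple imputation; LOCF as sensitivity |

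Nothing in the protocol closes the gap between the second and fifth rows.

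**Step 2: reproduce the plan's sample size (3.5).** Inputs: two-sided alpha 0.05, power 80%, effect 0.7 SD, baseline correlation 0.3, dropout 30%.
- Two-sample t-test: 33.02, rounded up to 34 per group, 68 in total.
- ANCOVA reduction: (1 − 0.3²) × 68 = 61.88, rounded up to 62.
- Dropout: 62 × 1.3 = 80.6, which matches the stated 80 within rounding. Dividing instead, 62 / 0.7 = 88.6, gives 89 and does not match. How the allowance was applied is a separate matter.

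**Step 3: the ceiling on missing values.** 0.30 × 80 = 24 subjects, leaving 56. Section 3.5 applies the 30% to the whole study, which runs to Month 6, and does not split it by cause. The number removed for non-compliance, outside treatment or violations before Week 5 is therefore some unknown part of 24.

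**Step 4: what observed data are worth under the plan's own inputs.** The residual-scale effect is 0.7 / √(1 − 0.09) = 0.734. The t-test power by number with an observed Week 5 VAS is:

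| Observed per arm | Total | Power |
|---|---|---|
| 28 | 56 | 76.9% |
| 31 | 62 | 81.1% |
| 40 | 80 | 90.0% |

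These rows use observed values only, ignore what imputation might recover, and assume the effect is 0.7 SD in removed subjects too. If it is smaller in them, the gain from retaining them is smaller.

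**Step 5: possible bias (assumed inputs).** If a fraction m of one arm is unobserved and its true mean differs from the imputed mean by k SD, that arm's mean is biased by m × k. The range k = 0.25 to 0.5 is assumed.
- m = 10%: 0.10 × 0.25 = 0.025 to 0.10 × 0.5 = 0.05 SD.
- m = 30%: 0.30 × 0.25 = 0.075 to 0.30 × 0.5 = 0.15 SD.

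The target effect is 0.7 SD. The protocol supports no particular m or k, does not give the direction, and states no VAS standard deviation with which to convert these figures to millimetres.

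**The case against.** The best case for the plan is that its wording is permissive, not prohibitive. Section 3.4 promises efforts to obtain information and allows follow-up after discontinuation. Missing data have a primary method, a sensitivity analysis and a parallel per-protocol analysis. The VAS is also taken in Weeks 1 to 4, so many removed subjects would have post-baseline values to inform the imputation. Section 5.1 already foresees telephone or distributed questionnaires for the follow-up survey.

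Much of this stands, and it limits the point. Four stronger readings are tempting and should be resisted:
- *Sections 3.4 and 6.3.2 contradict each other.* They do not. Both can be followed; together they leave a collection gap.
- *The protocol never separates stopping treatment from leaving the study.* It partly does: 3.4 ends treatment alone after a harmful adverse event, and it mentions treatment and observation separately when recording reasons. The distinction is simply not carried over to non-compliance or violations.
- *Twenty-four primary values will be lost this way.* The 30% covers every cause over six months; withdrawn consent and loss to follow-up would remain under any wording.
- *All randomised subjects are affected.* The primary set is treated subjects; 3.4 classes those who stop before treatment as screening failures.

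What does not stand is that the existing text is enough. The promised effort names neither the VAS nor a visit. The Week 1 to 4 values help imputation only as far as they explain why the later value is missing. The remote contact in 5.1 concerns healthcare use and quality of life, not the Week 5 VAS.

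**Conclusion.** The point holds as a cheap improvement. For treated subjects removed for non-compliance, outside treatment or protocol violations, the protocol permits avoidable missingness in the primary endpoint that may be related to outcome or arm. This conclusion rests on the text alone and does not depend on the sample size calculation.

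Its size is unknown. It lies between no subjects and the all-cause ceiling of 24 of 80. The bias of 0.025 to 0.15 SD is an illustration on assumed inputs, and the power figures assume a constant effect. A reader might infer that the primary result is already compromised; the documents do not support that, because removal and the end of follow-up are both discretionary and may seldom occur together. Ending follow-up after withdrawal of consent is proper and is no part of the finding.

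**What to change.** Amend 3.4 and 15.2 to say that, for subjects treated at least once who gave valid consent, non-compliance, outside treatment, eligibility violations and other protocol violations do not by themselves end outcome collection.

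In 3.4, replace the permissive follow-up sentence with a requirement, for example: *follow-up will continue at Visits 10, 11 and 12 unless the subject withdraws consent, valid consent was never obtained, or continued assessment is judged not to be in the subject's interest.* The second exception is needed because 15.2 counts missing consent among serious violations; the third respects the patient-interest ground in 3.4. If attendance is impossible, obtain at least the Week 5 VAS and the questionnaires remotely, with the VAS form sent in advance.

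Such violations then affect only the per-protocol set. The rules on when study treatment stops, and the screening-failure rule for untreated subjects, are left unchanged. The cost is a wording amendment and some extra contact effort at visits already scheduled.

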### 5.5.2. Concomitant Therapy

During the treatment period (week 1-4), medications and treatments from other medical institutions for temporomandibular joint (TMJ) disorders are not allowed. These treatments are permitted during the observation period. Any treatments received during the follow-up period should be recorded at the final visit.

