### 5.5.3. Prohibited Medications

- From study registration until the primary endpoint at week 5 (visit 10), all direct treatments aimed at relieving TMJ pain (e.g., medications, surgeries, other types of acupuncture, and physical therapy) are prohibited for both the clinical study group and the control group. No treatment restrictions are applied during the observation period after the primary endpoint at week 5.

However, during the study period, rescue medication such as acetaminophen (e.g., Tylenol, Acetaminophen tab) will be allowed for all clinical study subjects up to a maximum of 4g per day, and the usage of this medication will be recorded through self-reporting.

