#### 5.5.4. Subject Management During the Follow-Up Period After Treatment Completion

- Clinical study subjects who do not feel completely cured by the final visit or those who experience a recurrence of pain after the treatment completion visit will be allowed to receive treatment at a medical institution of their choice. The details of such treatments will be recorded during the follow-up visits.
- In preparation for any unexpected delayed adverse reactions, subjects will be allowed to seek medical care at any time under the researcher's instructions.

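### Section 3.4 lets investigators discontinue subjects for outside care that sections 5.5.3 and 5.5.4 permit after Week 5, and does not commit to following them afterwards

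*Protocol*

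**What the plan says.** Section 3.4 has a list introduced by "Other reasons for discontinuation of the clinical study by the investigator include". One entry covers operations, interventions and also "treatments with drugs that could affect the study outcome without the direction of the attending physician during the treatment period or follow-up period". On what happens next, the same section promises that "Efforts will be made to obtain information on patients who discontinue the clinical study", and adds: "For study subjects whose participation is discontinued, follow-up may continue with patient consent". Follow-up stops if consent is withdrawn.

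Three later sections deal with outside care over the same months:

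- Section 5.5.3 prohibits direct treatment of TMJ pain from registration to Visit 10 (Week 5), apart from acetaminophen as rescue. It then says: "No treatment restrictions are applied during the observation period after the primary endpoint at week 5".
- Section 5.5.4, headed "Subject Management During the Follow-Up Period After Treatment Completion", says that subjects who are not fully cured, or whose pain returns, "will be allowed to receive treatment at a medical institution of their choice". Details are to be recorded at the follow-up visits.
- Section 5.5.2 bans outside TMJ treatment in weeks 1 to 4, permits it in the observation period, and says: "Any treatments received during the follow-up period should be recorded at the final visit".

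**The concern.** After Visit 10, one section treats undirected outside care as a reason to remove a subject, while three others allow it, record it, or both. A site that reads section 3.4 literally can remove a subject for doing what section 5.5.4 says that subject may do.

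This matters because care after Week 5 is part of what the trial sets out to measure. Section 5.1 describes a survey to 6 months covering healthcare use and quality of life. Section 6.2 collects the treatments received and their costs. Section 6.3.3 makes the incremental cost-effectiveness ratio, with QALYs from the EQ-5D-5L, the primary economic endpoint.

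Section 5.5.4 names the people expected to seek care: those not cured and those who relapse. Removing them without further follow-up would selectively take poorer responders out of the Month 3 and Month 6 data. The trial is open-label for practitioners and participants and runs at five sites, so a discretionary rule with contradictory wording could also be applied unevenly.

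**Working it through.** The plan states no figure on this point. The check compares the texts and then counts the scheduled assessments at stake.

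**Step 1: the rules by period**

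| Period | Section 3.4 | Sections 5.5.2 to 5.5.4 | Consistent? |
|---|---|---|---|
| Registration to last session (weeks 1–4) | Undirected outside treatment is a ground | Outside TMJ treatment banned | Yes |
| Last session to Visit 10 (Week 5) | Still a ground | Still banned by 5.5.3 | Yes |
| After Visit 10 to Month 6 | Still a ground | Permitted by 5.5.2, 5.5.3 and 5.5.4, and recorded | **No** |

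**Step 2: can the texts be reconciled?**

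- *By the qualifier about the attending physician.* No. Section 5.5.4 gives free choice of institution for uncured or returning pain and asks for no direction. Only its separate item on delayed adverse reactions mentions the researcher's instructions.
- *By reading follow-up in 3.4 as only the days up to Visit 10.* No. The Summary of Protocol counts 3 follow-up visits over 24 weeks, and section 5.5.4 uses the same term in its heading for the time after treatment ends.

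**Step 3: what a removed subject could lose**

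Take a subject removed after Visit 10 and before Month 3 who is not followed further. Assessments lost are those scheduled at Month 3 and Month 6 (timetable; sections 6.1 and 6.2).

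| Assessment | Scheduled times | Total | Lost |
|---|---|---|---|
| Follow-up visits | Week 5, Months 3 and 6 | 3 | 2 |
| VAS | Weeks 1, 2, 3, 4, 5, Months 3 and 6 | 5 + 2 = 7 | 2 |
| PGIC | Week 5, Months 3 and 6 | 3 | 2 |
| EQ-5D-5L | Weeks 1 and 5, Months 3 and 6 | 4 | 2 |
| Medical costs | Weeks 1 and 5, Months 3 and 6 | 4 | 2 |
| Primary VAS | Week 5 | 1 | 0 |

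The EQ-5D-5L row follows the timetable and section 6.2. Section 5.1 lists only Visits 2, 10 and 12 for quality of life, which would make the loss 1 of 3. On either schedule the Month 6 value is lost.

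**Step 4: consequences in the analysis (section 6.3.2)**

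- Primary analysis at Week 5: unaffected once Visit 10 is done. The sample size in section 3.5 rests on this endpoint and does not change.
- Main analysis set: the subject stays in, because it includes everyone treated at least once. The Month 3 and Month 6 values behind the 6-month AUC and the QALY would be multiply imputed, after a loss triggered by the care itself.
- Per-protocol set: the subject leaves it, because it keeps only those who completed without dropping out.

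**The case against.** The strongest reply is that the specific rules already govern. Three sections permit or record care after Week 5, and section 5.5.4 plainly expects these subjects at the follow-up visits. Against them stands one entry in a list of possible reasons, which gives the investigator a power and imposes no duty. A site would have to use that power against explicit instructions before any harm followed. This stands as a limit on the likelihood of harm. It does not remove the contradiction, since nothing in the protocol says which section prevails.

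Second, part of the entry's reach into follow-up is proper. Week 5 is itself a follow-up visit and the 5.5.3 ban still runs until then. This is right, and it is why the phrase should be bounded and not deleted.

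Third, the conditional wording on continued follow-up can be read as depending only on the patient's consent, next to a promise of efforts to obtain information. That is a fair reading, but it still commits no one to the Month 3 and Month 6 assessments. Section 15.2, which lets subjects meeting drop-out criteria be dropped, points the other way. It reaches permitted care only through the 3.4 entry, so it adds no independent route to loss.

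Finally, the primary endpoint is untouched and no frequency can be given. Both are true, and they keep the point well short of a threat to the trial's main result.

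**Conclusion.** The concern holds. For the time after Visit 10, section 3.4 contradicts sections 5.5.2, 5.5.3 and 5.5.4, and its follow-up wording leaves later assessments uncommitted for anyone removed on this ground. Before Visit 10 the ground is sound.

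The exposure per affected subject is at most the two post-Week 5 visits, with the counts given above. These are counts of scheduled assessments, not an estimate of bias. How many subjects would be affected cannot be derived from the protocol. Harm requires both that a site uses the discretionary ground after Visit 10 and that it then stops following the subject. That care-seekers are the poorer responders is an inference from section 5.5.4, which describes them as uncured or relapsing.

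The results at risk are the Month 3 and Month 6 outcomes, the 6-month AUC, the QALY and cost comparison, and the per-protocol set. The change should be made, because it is nearly free and prevents a loss related to outcome.

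**What to change.** 1. **Section 3.4, the ground.** Limit it to the time from registration until the Visit 10 assessments are complete, matching section 5.5.3. Do not simply strike out the reference to follow-up: the ground should still cover the days between the last session and Visit 10.
2. **Section 3.4, follow-up.** State that subjects who stop study treatment or use outside care will, with their consent, continue all scheduled assessments to Month 6.
3. **Section 5.5.2, consistency only.** Let the ban on outside TMJ treatment run until the Visit 10 assessments are complete. Sections 5.5.2 and 5.5.3 read together already permit no day before Visit 10, so this only tidies the wording.

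The cost is three reworded sentences in one amendment with IRB approval (section 15.4) and a note to sites. It adds no visits, subjects or form fields.
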